#### The mid-arm circumference

The MAC will be measured using the midpoint between the olecranon and the acromion, with the arm extended, the muscles relaxed and the palm facing the thigh. The measurement will be recorded in centimetres, using the left hand. The participants will be classified as malnourished if the MAC is less than 24 cm and well-nourished if it is more than 24 cm [64].

#### Triceps skinfold thickness

The TSF will be measured to estimate the fat mass in millimetres. A VirtuFits digital fat calliper will be used to measure the skinfold of the triceps of the left arm. The test will be repeated three times, and the average will be recorded.

#### The mid-arm muscle circumference

The MAMC will be calculated according to the following formula: MAMC (cm) = MAC (cm) − (3.14 × TFS × 0.1). Guided by Symreng [65], malnutrition will be indicated for women up to 79 years of age if the arm muscle circumference is less than 19 cm and for women over 79 years if the arm muscle circumference is less than 18 cm. Malnutrition will be indicated for men up to 79 years if the arm muscle circumference is less than 23 cm and for men over 79 years if the arm muscle circumference is less than 21 cm.

#### Handgrip strength

Handgrip strength will be measured using the Saehan Hydraulic Hand Dynometer and recorded to the nearest 0.5 kg for both the dominant and non-dominant hands. Following the manufacturer’s recommendations, the participant will sit with the shoulder adducted and naturally rotated, the elbow flexed at 90° and the forearm and wrist in a neutral position. The test will be repeated three times for each arm, and the average value for each arm will be recorded.

#### Knowledge of nutrition

Participants’ nutritional knowledge will be measured by questions asking them what they think would provide them with the most protein and energy among different kinds of food, such as apples, vegetables, meat, oat crackers and dairy products. For example, one of the questions is as follows: ‘Which of the following food categories do you believe is best for you to consume to ensure a good start to your rehabilitation: dairy products with little or a lot of fat?’ The inclusion group will be able to find answers to the questions through the educational video.

#### Readmissions after discharge from the hospital

Readmissions to the hospital will be measured for up to 3 months after discharge by each department’s internal data collector, who will have access to the department’s record system.

### Data management and monitoring

#### Data analysis

For statistical analysis, SPSS version 28.01 (IBM Corp., Armonk, NY, USA) will be used. The statistical analysis plan will be based on the principles of the intention-to-treat approach. All ratio–interval scaled data will be tested for distribution using the *F*-test. When normally distributed, parametric statistical methods will be applied, such as Student’s *t*-test and the one-way analysis of variance (ANOVA). The data will be presented through means, standard deviation (SD) and 95% confidence limits. Normal or ordinal data will be presented as absolute numbers and frequencies. Differences will be determined using non-parametric tests (e.g. the *X*^2^-test, Mann–Whitney test and rank-sum test). The data from the RAND 36 questionnaire will be decoded using the SF-36 ordinal subscales and will be transformed into a ratio scale using the syntax SF-36 manual. The results will be presented from each of the eight subscales and the two main scales. The reliability of the SF-36 scales will be calculated using Cronbach’s alpha. When the data analysis is complete, the code regarding participants’ allocation to either the intervention or control groups will be revealed. Data will be collected as long as patients are included in the study. If patients withdraw their consent, data collection will stop. Deviation from the protocol will be registered and reported accordingly. Concerning post-assignment attrition, we will conduct an attrition analysis based on variables such as the participants’ gender, age, education level, marital status and help from home care. The attrition analysis will thus reveal any systematic loss at follow-up and identify whether there are participants with a higher likelihood of attrition.

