### Sample size

We base our calculation of the sample size on the effect estimates of the primary outcome of the combined physical scale from the feasibility study, as estimates were not available in the literature [53]. Alpha was set at 0.05, and the beta was set at 0.20. The estimated effect size was calculated to be 7 points on a scale ranging from 0 to 100, and the standard deviation of the population outcome was 18. The patients will be distributed with 50% in the control and intervention groups. Using the sample size-means calculator [56], the necessary sample size was calculated to be 104 in each of the 2 groups. Based on the feasibility study [53], we estimated a drop-out rate of 32%. Therefore, we need to recruit 138 participants for each group.

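### The F-test is named as the check of distribution that opens the way to parametric analysis, but it compares variances and is not a valid normality check; the practical effect is small.

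*Protocol article*

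**What the plan says.** The Data analysis section of the protocol article sets out the rule in consecutive sentences. First: "All ratio–interval scaled data will be tested for distribution using the *F*-test". Then: "When normally distributed, parametric statistical methods will be applied, such as Student’s *t*-test and the one-way analysis of variance (ANOVA"). After a sentence on how nominal or ordinal data will be presented, it adds "Differences will be determined using non-parametric tests", with chi-square, Mann–Whitney and rank-sum tests as examples. No other check of distribution is named.

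The primary outcome falls under this rule. The same section says that the RAND 36 data "will be transformed into a ratio scale using the syntax SF-36 manual", and that eight subscales and two main scales will be reported.

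The Sample size section is built on means of the combined physical scale: "The estimated effect size was calculated to be 7 points on a scale ranging from 0 to 100". It pairs this difference with an assumed SD of 18.

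**The concern.** A two-sample F-test asks whether two variances are equal, and it assumes normality in order to do so. It does not ask whether the data are normal. The condition in the second sentence therefore does not follow from the test in the first. If a check of equal variances was meant, the condition on normality is the error; if a check of normality was meant, the named test is the error.

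Two things are at stake. The gate can send data down the wrong branch in either direction. And the form of the primary comparison stays open until the outcome data have been split by arm, which a variance-ratio test requires. With ten RAND 36 scales to report, the method could differ from scale to scale for reasons unrelated to shape. If the other branch is a rank test, it does not estimate the mean difference for which the trial was sized.

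**Working it through.** **Inputs from the Sample size section.** "Alpha was set at 0.05, and the beta was set at 0.20"; difference 7 points; SD 18; 104 evaluable per group; 138 recruited per group; drop-out 32%. Allocation is 1:1 (Study design).

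**Assumptions, not from the documents.** Two-sided testing (the sidedness is not stated, but two-sided reproduces the sample size); the F-test applied at 5%; all the distribution shapes below; the second SD of 24.

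**Step 1: reproduce the plan's figure.** n per arm = 2 × SD² × (z₀.₉₇₅ + z₀.₈₀)² / δ² = 2 × 18² × (1.960 + 0.842)² / 7² = 103.8, so 104. This matches the plan; power at 104 is 0.801. The trial is thus sized for a comparison of means.

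**Step 2: sizes used.** 104 per arm is the stated evaluable number. 94 per arm is what the planned recruitment leaves after the stated drop-out: 138 × (1 − 0.32) = 93.8.

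**Step 3: how often does the F-test flag the data?** F = s₁²/s₂², two-sided at 5%. There were 20,000 simulated trials at 94 per arm and 10,000 at 104. Both arms share the same shape except in the unequal-SD row, where the true variance ratio is (24/18)² = 1.78. Shapiro–Wilk on one arm of 104 (1,000 samples) shows what a normality test would do.

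| Data | F-test, 94/arm | F-test, 104/arm | Shapiro–Wilk, 104 |
|---|---|---|---|
| Normal, equal SD | 4.8% | 4.8% | 4.9% |
| Two-peaked 0/25/50/75/100 score | 0.03% | 0.0% | 100% |
| Ceiling-skewed, beta(5, 1.5) | – | 6.8% | 100% |
| Lognormal, sigma 0.5 | – | 28.0% | 100% |
| Exponential | 30.6% | 30.7% | 100% |
| Normal, SD 18 v 24 | 79.1% | 82.6% | 4.4% |

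The two-peaked score had probabilities 0.45, 0.10, 0.08, 0.10, 0.27 at 94 per arm and 0.35, 0.10, 0.10, 0.10, 0.35 at 104. Exponential data pass as normal in 100 − 31 = about 69% of trials.

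**Step 4: what happens to the trial's inference?** Take the rule in its fullest form: Mann–Whitney if the F-test rejects, otherwise the pooled t-test (10,000 trials per cell).

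| Scenario | Type I error of whole rule, 94 / 104 |
|---|---|
| Normal, equal SD | 0.048 / 0.053 |
| Normal, SD 18 v 24 | 0.054 / 0.054 |
| Two-peaked score | 0.050 / 0.049 |
| Exponential | 0.032 / 0.033 |

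| Power for 7 points | Whole rule | Always t-test | Difference |
|---|---|---|---|
| Normal, equal SD, 94 | 0.761 | 0.763 | −0.002 |
| Normal, equal SD, 104 | 0.795 | 0.797 | −0.002 |
| SD 18 v 24, 94 | 0.601 | 0.619 | −0.018 |
| SD 18 v 24, 104 | 0.644 | 0.664 | −0.020 |
| Exponential shift, 94 | 0.85 | 0.75 | +0.10 |

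The plain t-test at 104 per arm had type I error between 0.046 and 0.051 in every scenario tried in Step 3, unequal SDs included.

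**The case against.** The strongest reply is that a wrong gate need not produce a wrong result. A reader might infer from the first table in the working that the trial's conclusions would be unreliable. The later tables do not support that: error is not materially inflated, and power falls by about 2 points at worst. The commonest misfire, a non-normal score passed as normal, leads to a t-test, which is harmless at about 100 per arm and close to the remedy proposed here. This stands, and it limits the weight of the point.

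Three other strong readings also fail:

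- That the F-test is blind to non-normality. It reacts to heavy tails, in 28% to 31% of the lognormal and exponential trials. That is a by-product, and too weak for the purpose.
- That unequal SDs make a Welch or robust standard error necessary. With 1:1 allocation the pooled t-test held about 5% even at 18 v 24.
- That the protocol sends ratio-scaled data that fail the check to a Mann–Whitney test. No sentence says so. The non-parametric sentence follows one that reads normal or ordinal, where nominal is evidently meant, and its examples include chi-square. The condition on normality implies some alternative, but leaves it unnamed.

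It can also be said that details belong in a statistical analysis plan that is not shown. That covers robust errors and sensitivity analyses. It does not cover this rule, which the article states and states wrongly.

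**Conclusion.** The point holds as a moderate-to-minor correction. The F-test is not a valid normality check, and the article makes parametric analysis depend on it. As a gate it misfires in both directions: almost no two-peaked scores and only about 31% of exponential samples are flagged, against 79% to 83% of normal samples with SDs of 18 and 24. The primary RAND 36 comparison is left to a choice made from the data, with the second branch only implied, in a trial sized for a mean difference.

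The cost to inference is small: type I error of about 0.03 to 0.054 and a power loss of up to about 2 points. These figures rest on illustrative shapes, an assumed second SD of 24, 94 to 104 patients per arm, and the reading that a rejected F-test leads to Mann–Whitney. The two-peaked score resembles a coarse subscale more than the combined physical scale used for sizing, so the primary score itself may well be closer to normal. That the F-test is the wrong tool for checking distribution depends on none of these assumptions.

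**What to change.** Delete the F-test sentence and the condition that follows it. State instead that the primary analysis is the between-group difference in mean RAND 36 physical summary score at 3 months, with 95% CI, adjusted for the baseline score and applied whatever the distribution. The Measurements section already has all measurements taken in hospital as well as at 3 months, so adjustment needs no new data. Any rank-based analysis should be labelled a sensitivity analysis. Robust or bootstrap standard errors are optional. In the same edit, correct the nominal/ordinal sentence so that it is clear which data the chi-square and rank tests are for.

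The cost is one or two sentences, with no change to sample size, data collection or conduct. The change should be made, and recorded in the registry as the Monitoring section provides for protocol changes, before outcome data are compared by arm.

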### Measurements

The measurements will mainly focus on basic information, health-related quality of life, body composition measurements and readmission to hospital. The same externally trained data collector will carry out all measurements during the patients’ hospital stays and 3 months after discharge. We will register the number of readmissions within 3 months after discharge from the hospital. Figure 1 shows the schedule for enrolment, the intervention and the assessment of the trial according to the SPIRIT template.

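### The tests named for the primary outcome take no baseline covariate, although RAND 36 is measured in hospital and again at 3 months; an ANCOVA on baseline would be more precise at almost no cost.

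*Protocol article*

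**What the plan says.** Under Measurements, health-related quality of life is listed with the body composition measurements, and the timing is stated for all of them: "The same externally trained data collector will carry out all measurements during the patients’ hospital stays and 3 months after discharge". A baseline RAND 36 score is therefore collected.

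Under Data analysis, for normally distributed data, "parametric statistical methods will be applied, such as Student’s *t*-test and the one-way analysis of variance (ANOVA". For other data the section names chi-square and rank tests. It names no analysis of covariance, regression or other method with a baseline covariate, and it does not say whether the 3-month score or the change from baseline is compared. It states that the statistical analysis plan will follow intention-to-treat principles. It also plans a comparison of participants lost to follow-up on an open list of variables, and says of it: "The attrition analysis will thus reveal any systematic loss at follow-up".

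Under Sample size, the calculation rests on the RAND 36 combined physical scale, with a 5% alpha, 80% power, a target difference of 7 points and two groups of equal size. On the spread it says that "the standard deviation of the population outcome was 18". This SD is that of the outcome, with no allowance for a baseline correlation. The result is that "the necessary sample size was calculated to be 104 in each of the 2 groups". A drop-out of 32% is expected and the recruitment target is 138 per group.

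**The concern.** The aim is to prevent a loss of health-related quality of life, so each participant's starting level is part of the question, and the trial collects it. Participants come from three surgical departments with very different case mixes. The Randomisation section describes complete randomisation and mentions no stratification. Variation between patients in starting health and type of surgery then stays in the error term of the named tests.

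What is at stake is precision. Chance imbalance in an unadjusted comparison is already covered by its standard error, so the confidence interval is valid but wider than it needs to be. This matters in a trial that expects to lose about a third of its participants.

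**Working it through.** **Inputs from the protocol article.** Difference 7, SD 18, alpha 0.05 (two-sided assumed, since the text does not say), power 80%, 1:1 allocation, 104 per group, 32% drop-out, 138 recruited per group (all from Sample size).

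**Assumption.** r, the correlation between baseline and 3-month RAND 36, is not given. The range 0.3 to 0.7 is shown.

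**1. Reproduce the plan's figure.** n per group = 2 × [(1.960 + 0.842) × 18 / 7]² = 103.8, so 104. This matches the plan as an unadjusted two-sample comparison. Sample size and named tests therefore agree with each other, and both leave the baseline out.

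**2. Expected completers.** 138 × (1 − 0.32) = 93.8, about 94 per group.

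**3. Unadjusted precision.** Standard error = 18 × √(2/94) = 2.63 points. Power for 7 points with a two-sided t-test is 75.6%. (The shortfall from 80% comes from how 104 was inflated for drop-out: 104 × 1.32 ≈ 138, whereas 104 / 0.68 ≈ 153. That is a separate matter; here 94 is only the common starting point.)

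**4. Baseline-adjusted precision.** Residual SD = 18 × √(1 − r²); power from the same t calculation with 94 per group.

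| Assumed r | 1 − r² | Residual SD | n per group for 80% power | Power, 94 per group |
|---|---|---|---|---|
| 0 (unadjusted) | 1.00 | 18.00 | 104 | 75.6% |
| 0.3 | 0.91 | 17.17 | 95 | 79.4% |
| 0.5 | 0.75 | 15.59 | 78 | 86.5% |
| 0.7 | 0.51 | 12.85 | 53 | 96.0% |

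With 94 per group, power reaches 80% at r of about 0.32. The normal approximation gives figures within half a percentage point of these.

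**5. Would a t-test on change scores do as well?** With equal SDs at both times, the variance of a change score is 2(1 − r) times that of the 3-month score: 1.4 at r = 0.3, 1.0 at r = 0.5 and 0.6 at r = 0.7. It is therefore less precise than the 3-month score alone when r is below 0.5. Against ANCOVA, 2(1 − r) − (1 − r²) = (1 − r)², which is never negative. The change score is thus never more precise than ANCOVA.

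**The case against.** **The list of tests is open.** It is introduced as examples, and a t-test could be run on change scores, so the text does not strictly fix an analysis that ignores baseline. This stands as a reading of the words. It does not remove the point: no covariate-adjusted method is named, the sample size assumes none, and the change-score route does not recover the precision.

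**An unadjusted comparison is valid and matches the sample size.** This stands. The point is about efficiency, not bias.

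**The gain depends on a correlation that the document does not give.** This also stands. Baseline is measured in hospital after surgery, so r could be low. At r = 0.3 the gain is under 4 percentage points of power.

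**Stronger readings that the document does not support.** Because about a third of outcomes may be missing and the named tests need a 3-month value, a reader might infer that the plan specifies a completers-only analysis and so contradicts its intention-to-treat statement. It does not say so. No completer set is defined, intention-to-treat mainly means analysing participants as randomised, and handling of missing outcomes may sit in an analysis plan that is not shown. A reader might also infer that the attrition analysis is confined to the five characteristics it lists; the wording offers them as examples. Finally, a mixed model for all randomised participants might seem to bring drop-outs into the comparison. With a single follow-up, participants who have only a baseline value add essentially nothing to the estimated arm effect, so that is no reason to prefer it to ANCOVA.

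**Conclusion.** The point holds as one of precision. The protocol article collects baseline RAND 36 but names only tests that cannot adjust for it, and sizes the trial in the same way. Adjustment would cut the outcome variance by 9%, 25% or 51% at r = 0.3, 0.5 or 0.7. With 94 completers per group, power for 7 points would rise from about 76% to about 79%, 86% or 96%.

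These figures rest on the assumed r, on the plan's SD of 18 and 32% drop-out, and on two-sided testing. They credit nothing to adjustment for department. The comparison with change scores also assumes equal SDs at the two times. The finding does not show bias in the planned comparison, nor a breach of intention-to-treat.

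**What to change.** In Data analysis, name the primary analysis as an ANCOVA of the 3-month RAND 36 combined physical score on trial arm, baseline score and surgical department, reporting the adjusted mean difference with its 95% confidence interval. Use the same model, with each outcome's own baseline value, for the continuous secondary outcomes.

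Add trial arm and baseline RAND 36 to the variables in the attrition analysis. Its open list already allows this, and both are needed to see whether loss differs between arms or by starting health.

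The cost is a change of wording before the data are analysed. The baseline measurements are already planned, the recruiting department is known for each participant, and SPSS, the software named in the article, fits the model.

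### Nutrition knowledge: answers analysed as collected would go to unadjusted item-level tests, and no named test takes the inclusion answers as a covariate; one pre-keyed number-correct score would be better

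*Protocol article*

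**What the plan says.** Under Knowledge of nutrition, the article states: "Participants’ nutritional knowledge will be measured by questions asking them what they think would provide them with the most protein and energy". The one example is a choice between two options, "dairy products with little or a lot of fat". The same paragraph adds: "The inclusion group will be able to find answers to the questions through the educational video". So the questions have intended answers. No score is named, and the number of questions is not given.

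The Abstract (Method) has knowledge measured at inclusion and at the 3-month follow-up. The Hypotheses section lists it twice among the data meant to verify the hypothesis.

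The Data analysis section assigns methods by type of data, not by outcome:

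- Ratio or interval data: "When normally distributed, parametric statistical methods will be applied, such as Student’s" *t*-test and one-way ANOVA.
- The other type: "Normal or ordinal data will be presented as absolute numbers and frequencies". Here 'Normal' is evidently a slip for 'Nominal'.
- Then: "Differences will be determined using non-parametric tests", with the chi-square, Mann–Whitney and rank-sum tests as examples.

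No data type or test is assigned to knowledge, and the section states no multiplicity rule.

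**The concern.** Other outcomes built from raw values come with a stated construction. RAND 36 items become eight subscales and two main scales, BMI and MAMC have formulas, and skinfold and grip strength are averages of three readings. Knowledge is left as a set of questions. A two-option food choice is nominal, so an analyst who takes the answers as collected is led to frequencies and a separate test per question, each at the usual level.

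Knowledge is the direct target of the video and the first link in the hypothesised chain. Uncorrected item tests could let one chance item be reported as a knowledge gain. They could also miss a modest gain spread over all the questions. For any question with three or more options, a chi-square test also responds to a move from one wrong food to another.

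**Working it through.** **Inputs**

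- Level per test: 0.05. The Sample size section says "Alpha was set at 0.05, and the beta was set at 0.20" for the primary outcome; the same two-sided level is assumed for item tests.
- Analysed per arm: 104 (stated requirement), or 138 × (1 − 0.32) = 93.84, about 94 (stated recruitment less stated drop-out).
- Not in the article, so assumed: K = 5 or 10 questions; 50–70% correct in the control arm; gains of 10–25 points; inter-item correlation r = 0.1–0.3.

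**1. The plan's own figure.** n = 2(1.960 + 0.842)² × 18² / 7² = 103.8, so 104 per group. The stated number reproduces with a two-sided 0.05 (one-sided gives 82). The article gives no power figure for knowledge.

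**2. False positives if K items are tested separately and the video does nothing.** For independent items the chance of at least one significant item is 1 − 0.95^K. Counting only results that favour the video, it is 1 − 0.975^K.

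| K | Either direction | Favouring the video |
|---|---|---|
| 5 | 0.226 | 0.119 |
| 10 | 0.401 | 0.224 |

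Simulations with correlated items gave about 20–22% (5 items) and 31–39% (10 items) in either direction. A single total-score *t*-test stayed at 4–6%.

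**3. Power of one item.** With gain d and mean proportion p̄,

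power = Φ{[d − 1.96√(2p̄(1−p̄)/n)] / √([p₁(1−p₁)+p₂(1−p₂)]/n)}.

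For 60% against 70% at 94 per arm: (0.10 − 1.96 × 0.0696)/0.0692 = −0.53, so power is 0.30. Over control rates of 50–70%:

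| Gain | 94 per arm | 104 per arm |
|---|---|---|
| +10 points | 0.28–0.35 | 0.30–0.38 |
| +15 points | 0.55–0.70 | 0.59–0.74 |
| +20 points | 0.80–0.94 | 0.84–0.96 |
| +25 points | 0.95–0.997 | 0.97–0.998 |

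**4. Power of one score.** The SD of the proportion correct is √{p̄(1−p̄)[1+(K−1)r]/K}. For K = 5, r = 0.2 and 50% against 60%: √(0.2475 × 1.8/5) = 0.298. At 94 per arm the standard error is 0.298 × √(2/94) = 0.0435, and 0.10/0.0435 − 1.96 = 0.34, so power is 0.63. A single item at the same rates has 0.28. For a 10-point gain on every item from 50%:

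| K | 94 per arm (r = 0.3 to 0.1) | 104 per arm (r = 0.3 to 0.1) |
|---|---|---|
| 5 | 0.55–0.74 | 0.59–0.78 |
| 10 | 0.62–0.89 | 0.66–0.91 |

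This advantage presumes that the gain is spread over the questions. A change confined to one question would be diluted in a sum.

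**5. Inclusion answers.** The named methods are the *t*-test, one-way ANOVA, chi-square, Mann–Whitney and rank-sum. None takes a baseline covariate, and the article does not mention analysing change. Adjustment multiplies the residual variance of the score by about 1 − ρ², where ρ is the correlation between inclusion and 3-month scores. The article does not give ρ, so no figure is put on this gain.

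**The case against.** A reader might infer that the plan prescribes question-by-question chi-square tests in place of a score. The text does not support that. The quoted rule is generic, covers ordinal data too, and gives its tests only as examples. A number-correct score would fit the same paragraph through Mann–Whitney, or through the *t*-test rule. A full protocol or statistical analysis plan, not shown, may define such a score, and its absence from an article is not in itself an error. This part of the objection stands, so the item-level consequence is conditional.

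Four further limits also stand:

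- **Direction.** In the two-option example the frequencies show which way answers moved. The lack of direction matters only for questions with three or more options, which the list of foods makes plausible but does not show.
- **Power.** It is low only for shifts of about 10–15 points.
- **Inclusion answers.** One might infer that they are to be discarded. The article does not say so; it names no method that takes them as a covariate, and its lists of methods are open.
- **'Normal' for 'Nominal'.** Read literally, it collides with the parametric rule for normally distributed data. The pairing with ordinal data and frequencies makes the meaning plain, so the slip is editorial.

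The objection does not show that the named methods are as good as one adjusted score. Even if a score is formed, none of them takes the inclusion score as a covariate.

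**Conclusion.** The point holds in a limited form. Analysed as collected, the answers fall under a rule that leads to item frequencies and unadjusted item tests, although the article neither states item-by-item testing nor rules out a score. If items are tested separately without correction, the chance of at least one false-positive item is about 20–40% for 5–10 questions. It is about 12–22% counting only results that favour the video, under independence. Single-item power is about 0.3 for a 10-point shift and about 0.8 or more for 20 points. These figures rest on assumed item counts, correct rates, effects and correlations.

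On either reading, a single baseline-adjusted score improves on the methods named. The matter concerns a secondary outcome and leaves the RAND 36 analysis untouched.

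**What to change.** In Knowledge of nutrition and Data analysis:

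1. Mark each question right or wrong against a key taken from the video script and fixed before the arms are compared.
2. Sum the marks to a number-correct score.
3. Compare the 3-month score between arms once, with the inclusion score as covariate (ANCOVA), and report the mean difference with its 95% confidence interval.
4. Show item frequencies as description, without tests.
5. Correct 'Normal or ordinal' to 'Nominal or ordinal'.

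The cost is a few sentences and a one-page key, with no new data, visits or staff. The small downside is that questions with no defensible right answer must be left out of the score.
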